### Subject selection

A retrospective cohort study of consecutive patients treated at 17 vascular centres is to be performed. All patients are eligible and the opt-out procedure will be used to allow patients to object to participation within 4 weeks, which is in accordance with the Dutch Code of Civil Procedure. The Medical Ethics Review Committee of the Amsterdam UMC, location Academic Medical Centre, Amsterdam, has confirmed that the Medical Research Involving Human Subjects Act (WMO) does not apply to our study. This study is conducted according to the General Data Protection Regulation (AVG 2016) and the Medical Treatment Agreement Act (WGBO).

### Data sources

Paper or electronic medical records are used in order to identify participants who match study-defined criteria.

### Primary and secondary endpoints

#### Main study endpoint

The number of patients with an intervention and aneurysm-related mortality classified for patients with and without yearly imaging surveillance.

#### Secondary study endpoints

Date, type, indication and outcome of all postoperative imaging during follow-up.Type I, type II, type II and type IV endoleak, graft or outflow (iliac) occlusion, endograft infection detected by postoperative imaging, if present.Date and type of intervention during follow-up, if present.Date of aneurysm rupture during follow-up, if present.Date of death during follow-up, if present.Costs of all EVAR-related imaging and outpatient clinic visits.

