### General study design

A multicentre retrospective cohort study in 17 medical centres in the Netherlands. Data will be collected from the medical records of all consecutive patients with AAA who underwent EVAR between January 2007 and January 2012. This selection provides a theoretical length of follow-up of 6–11 years on December 2018. Patients will be divided into three groups: (A) patients without abnormalities at their first postoperative CTA with yearly imaging surveillance, (B) patients without abnormalities at their first postoperative CTA without yearly imaging surveillance and (C) patients with abnormalities at their first postoperative CTA (figure 1). This retrospective design has the advantage of collecting long term follow-up data. The Dutch Dream trial found that the number of interventions starts to rise 4 years after EVAR and the long-term results of the EVAR-1 trial show that EVAR has an early survival benefit but inferior late survival compared to open surgical repair.^13 14^ This is in contrast to the recently published long-term results of the OVER trial in which no difference was observed between EVAR and OSR in the primary outcome of all-cause mortality.^15^ Hence, a prospective study would take approximately 8 to 10 years to gather enough patients with adequate follow-up.

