**Figure 1 F1:**
[figure not shown]
Patient subgroups. AAA, abdominal aortic aneurysm; CTA, CT angiography; EVAR, endovascular aneurysm repair.

The standard of care is defined by the current guidelines and IFU. The usual follow-up schedule in the IFU is: CTA and abdominal X-ray at 30 days, 6 and 12 months and yearly thereafter. The 2019 ESVS guidelines recommend a CTA 30 days after EVAR. If there is adequate seal and no endoleak, patients are classified as low risk and CTA follow-up may take place 5 years later. If there is an inadequate seal and endoleak type I/III patients could be either evaluated for re-intervention or if sac shrinkage occurs yearly DUS is recommended. In the 2018 SVS guideline, CTA at 1 and 12 months is recommended and if neither endoleak nor sac enlargement is documented, DUS is suggested for annual postoperative surveillance. In our study design, the definition of compliance is undergoing imaging surveillance every 16 months since patients in most centres will be rescheduled if they missed their annual follow-up visit. Device-specific complications after EVAR will also be examined.

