### Study procedures

The primary outcomes of this study are interventions and aneurysm-related mortality for patients who had a normal initial postoperative CTA and who do adhere to our definition of yearly imaging surveillance over a 6-year to 11-year follow-up period, compared to those who do not adhere to our definition.

Interventions are EVAR-related interventions defined by the SVS reporting standards as postoperative adjunctive manoeuvres.^16 17^ Interventions for wound complications at the access site are not included, since these are detectable without the use of imaging.

Date of death during follow-up, if applicable, will be obtained from patient medical records and verified by the Dutch municipal personal records database (GBA).

Details of all surveillance imaging are obtained from patient medical records and radiology reports. The time between imaging appointments is calculated to determine whether patients adhere to this studies definition of with yearly imaging surveillance, that is, within every 16 months.

Date, type, indication and outcome of all postoperative imaging during follow-up are obtained from patient medical records, specifically imaging order forms and radiology reports. A normal initial postoperative CT scan is defined as a CT scan which shows no endoleaks, endograft migration (>10 mm), kinking or obstruction. All imaging outcomes are based on the report compiled by radiologists. These reports will not be re-evaluated by an independent radiologist, since we want to base our outcomes on real life data.

Secondary outcomes are all-cause mortality, type I, type II, type III and type IV endoleak, graft or outflow (iliac) occlusion, aneurysm rupture and endograft infection. This is also obtained from patient medical records, specifically radiology reports and Dutch municipal personal records database (GBA).

Date of aneurysm rupture is obtained from patient medical records, specifically operative reports, radiology reports and progress notes.

Costs of all EVAR-related imaging and outpatient clinic visits will be calculated per patient. Cost is defined as volume times price. Prices from the ‘Cost manual of the Dutch Health Care Institute’’ will be used. Costs for the patients will also be included. The quality-adjusted life years, a generic measure of disease burden including both the quality and quantity of life, cannot be calculated with this retrospective design.

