### Statistical methods

Differences in baseline characteristics between patients undergoing or not undergoing yearly standardised imaging surveillance by either CTA or DUS, will be analysed using the χ^2^ or Fisher's exact test for categorical variables and the student's t-test or Mann-Whitney test for continuous variables, if appropriate.

The primary endpoints, that is, survival and freedom from intervention will be estimated by Kaplan-Meier survival analysis and differences between groups will be assessed with the log-rank test.

Secondary endpoints such as freedom from aneurysm rupture between patients with and without yearly standardised imaging surveillance will be estimated by Kaplan-Meier survival analysis, and differences between these groups will be calculated with the log-rank test.

Multivariable cox regression analysis will be used to determine survival and the freedom of intervention corrected for age, gender, AAA diameter, ASA classification, neck length, neck angulation and type of endograft. The association between postoperative intervention and the following covariates will be investigated with the multivariate Cox-regression analysis:

Age.Gender.AAA diameter.ASA classification.Neck length (>15 mm).Neck angulation (>60°).Type of endograft.Initial postoperative CTA.

All statistical analyses will be done with SPSS software (IBM, V.25). The level for statistical significance is set at a p value <0.05. The proportion of missing data will be displayed. The missing values will be imputed by multiple imputation techniques if this does not exceed 10%–15% and conduct a sensitivity analysis to investigate the effect of the missing data on the results of the analysis. If missing data on outcome variables exceeds 15%, we plan to perform subgroup analysis.

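### Endoleak, occlusion and infection found on scans are compared between groups defined by scan frequency, so the comparison cannot separate fewer complications from fewer detected complications

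*Protocol article*

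**What the plan says.** **Outcomes.** The Secondary study endpoints section lists "Type I, type II, type II and type IV endoleak, graft or outflow (iliac) occlusion, endograft infection detected by postoperative imaging, if present". Study procedures repeats the list: "Secondary outcomes are all-cause mortality, type I, type II, type III and type IV endoleak, graft or outflow (iliac) occlusion, aneurysm rupture and endograft infection". (The repeated type II in the first list is a slip, since the second list has type III. It does not affect this point.) Study procedures gives medical records, specifically radiology reports, as the source, and adds: "All imaging outcomes are based on the report compiled by radiologists". There is no independent re-reading. Dates of death are verified in the municipal registry.

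**Groups.** Under General study design, group A is "patients without abnormalities at their first postoperative CTA with yearly imaging surveillance". Group B also has a normal first CTA but no yearly imaging. The dividing rule follows Figure 1: "the definition of compliance is undergoing imaging surveillance every 16 months".

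**Comparison.** Statistical methods states: "Secondary endpoints such as freedom from aneurysm rupture between patients with and without yearly standardised imaging surveillance will be estimated by Kaplan-Meier survival analysis", with differences assessed by log-rank test. The Cox covariates listed there include neither the number nor the timing of scans.

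**Limitations.** The Discussion names record-based data, unnoticed transfer to other centres, changes in practice, attrition and survey bias. It does not name unequal detection.

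**The concern.** The exposure is how often a patient is imaged. For endoleak, occlusion and infection, imaging is also how the outcome is found. A silent finding in a patient who is not scanned is not recorded, one that resolves between two distant scans is never seen, and one that persists is dated late. All three effects act more strongly in group B.

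The protocol is aware of the mechanism. Study objectives expects adherence to surveillance to bring more abnormalities to light, and Study procedures leaves out interventions for access-site wounds because imaging is not needed to notice them. Neither remark is carried over to the comparison of these secondary outcomes.

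What is at stake is interpretation. A lower curve for endoleak or occlusion in group B could mean fewer complications or fewer examinations, and the planned test cannot tell which. The point does not apply to death, nor to rupture or other events that surface clinically.

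**Working it through.** The protocol gives no expected figure for endoleak, occlusion or infection. Its nearest figure, used here only for group size, is 719 per group in Sample size and power. This reproduces with two-sided alpha 0.05, 90% power and unpooled variance:

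n = (1.960 + 1.282)² × (0.75×0.25 + 0.82×0.18) / 0.07² ≈ 718.6, so 719.

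**Assumptions (not in the protocol).** The onset hazard is the same in both groups and gives 20% by 7 years. Findings either persist or resolve at 0.3 per year. A share present with symptoms and are detected at onset; the rest are found at the next scan while present.

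**Step 1: fixed scan intervals, no deaths.** Group A is scanned yearly, group B every 2, 3 or 5 years. The table shows the percentage detected by year 7.

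| Findings | Yearly | 2-yearly | 3-yearly | 5-yearly | Gaps (points) | Chance of p<0.05, 719 per group |
|---|---|---|---|---|---|---|
| All silent, persistent | 20.1 | 17.4 | 17.4 | 14.7 | 2.7, 2.7, 5.4 | 26%, 26%, 77% |
| All silent, resolving | 17.3 | 13.1 | 11.4 | 7.5 | 4.2, 5.9, 9.8 | 60%, 89%, 100% |
| Half symptomatic, persistent | 20.2 | 18.6 | 18.6 | 17.3 | 1.6, 1.6, 2.9 | 11%, 11%, 28% |
| All symptomatic | about 20 | about 20 | about 20 | about 20 | none | no excess |

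The first row can be checked by hand. The last scan by year 7 falls at year 6 (2- and 3-yearly) or year 5 (5-yearly), so detection is 1 − 0.8^(6/7) = 17.4% or 1 − 0.8^(5/7) = 14.7%. That gap in proportions therefore depends on the cut-off: at year 6, yearly, 2-yearly and 3-yearly scanning have found the same persistent findings, and only the dates differ.

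**Step 2: patients sorted by the 16-month rule.** Further assumptions: follow-up 6 to 11 years, deaths 2% per year, and mixed adherence (half the patients on time at 98% of scans, half at 50%; late gaps of 1.6 to 3.5 years). A patient with any gap above 16 months is in group B. There are 60,000 simulated patients, 47% of them in group A. The 7-year Kaplan-Meier detected incidence, A versus B, is:

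- all silent, persistent: 18.7% v 17.2%, gap 1.5 points
- all silent, resolving: 15.4% v 12.7%, gap 2.7 points
- half symptomatic: 19.2% v 18.1% (persistent) and 18.1% v 16.5% (resolving), gaps 1.1 and 1.6 points
- all symptomatic: about 20% v 20%

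**Sensitivity.** With all findings silent, the gap is 0.7 and 3.2 points at 8% annual deaths. If every patient is on time at 85% of scans, it is 0.1 and 1.5 points at 2% deaths, and 1.2 and 2.2 points at 8%. The simulation standard error of a gap is about 0.3 points: √(0.187×0.813/28,200 + 0.172×0.828/31,800) = 0.0031. In the all-symptomatic settings, where the gap is zero by construction, simulated gaps ran from −0.3 to +0.8 points.

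**Step 3: chance of a spurious result.** Treating the Step 2 figures as simple proportions with 719 per group:

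- 1.5 points: SE = √[(0.187×0.813 + 0.172×0.828)/719] = 0.0202; z = 0.015/0.0202 = 0.74; chance = Φ(0.74 − 1.96) ≈ 11%.
- 2.7 points: SE = √[(0.154×0.846 + 0.127×0.873)/719] = 0.0183; z = 1.47; chance = Φ(1.47 − 1.96) ≈ 31%.

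With no bias, the chance in that direction would be 2.5%. Censoring would lower both figures somewhat.

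**Step 4: crude proportions.** With silent, persistent findings, mixed adherence and 8% annual deaths, the crude detected proportions are 13.2% in A and 17.8% in B, the opposite direction. Patients with short follow-up have less time to miss a scan and are more easily classed as compliant.

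**The case against.** The strongest reply is that the biased test is inferred. Statistical methods names only rupture, which needs no surveillance to surface. Parts of the secondary endpoint list read as data items, and this is a condensed article. That limits the wording to coverage by implication, but does not remove the point. Study procedures calls these findings secondary outcomes, and the analysis sentence addresses secondary endpoints as a class, with rupture as an example.

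Three stronger readings are tempting, and the documents do not support them.

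- A reader might infer that group A is bound to show more events and that the bias always favours the study hypothesis. It does not follow. The excess disappears if all findings present with symptoms, and crude proportions can reverse.
- A reader might infer a spurious gap of 5 to 9 points. Gaps of that size need fixed, widely spaced scans in group B and no symptom-triggered imaging. The protocol instead places anyone outside the 16-month rule in group B and records all postoperative imaging. Its Background section cites 61% to 98% of interventions as prompted by symptoms. That figure concerns interventions, so it does not give the silent share of endoleaks, but it argues against assuming that every finding is silent.
- A reader might infer that fewer endoleaks in group B is a planned argument for safety. The stated hypotheses rest on interventions and aneurysm-related mortality; none predicts fewer endoleaks. The risk is one of misreading a result.

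It is also fair to object that yield per scan has its own bias, because group B scans may be enriched for symptom-driven imaging. That stands and shapes the fix.

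**Conclusion.** The concern holds as a biased comparison of some secondary outcomes. Exposure and ascertainment are the same process for endoleak, occlusion and infection found on scans. With equal true incidence, the Kaplan-Meier comparison tends to show more and earlier events in group A for findings that do not bring the patient to imaging.

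The size cannot be fixed from the protocol. Under the assumed 20% incidence, mixed adherence, the 16-month sorting and 2% annual deaths, it is about 1.5 to 2.7 points at 7 years if all findings are silent, less if some present with symptoms, and about 0 if all do. Roughly 3 to 10 points requires the fixed-interval, all-silent case. The direction is a tendency that depends on the silent and transient share. No sample size or primary endpoint figure changes.

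**What to change.** In Secondary study endpoints, Study procedures and Statistical methods:

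- Use the scan indication, which is already collected, to classify each endoleak, occlusion and infection as symptom-driven or surveillance-detected.
- Limit the A versus B log-rank tests of secondary endpoints to events that surface without surveillance imaging: rupture, symptomatic occlusion, clinically presenting infection and death.
- Report surveillance-detected endoleak, occlusion and infection descriptively by group. Split any yield per scan by scan indication.
- Add unequal detection between the groups to the limitations in the Discussion.

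The cost is wording and analysis only, with no new data collection. The downside is that a few secondary endpoints become descriptive.

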### Study procedures

The primary outcomes of this study are interventions and aneurysm-related mortality for patients who had a normal initial postoperative CTA and who do adhere to our definition of yearly imaging surveillance over a 6-year to 11-year follow-up period, compared to those who do not adhere to our definition.

Interventions are EVAR-related interventions defined by the SVS reporting standards as postoperative adjunctive manoeuvres.^16 17^ Interventions for wound complications at the access site are not included, since these are detectable without the use of imaging.

Date of death during follow-up, if applicable, will be obtained from patient medical records and verified by the Dutch municipal personal records database (GBA).

Details of all surveillance imaging are obtained from patient medical records and radiology reports. The time between imaging appointments is calculated to determine whether patients adhere to this studies definition of with yearly imaging surveillance, that is, within every 16 months.

Date, type, indication and outcome of all postoperative imaging during follow-up are obtained from patient medical records, specifically imaging order forms and radiology reports. A normal initial postoperative CT scan is defined as a CT scan which shows no endoleaks, endograft migration (>10 mm), kinking or obstruction. All imaging outcomes are based on the report compiled by radiologists. These reports will not be re-evaluated by an independent radiologist, since we want to base our outcomes on real life data.

Secondary outcomes are all-cause mortality, type I, type II, type III and type IV endoleak, graft or outflow (iliac) occlusion, aneurysm rupture and endograft infection. This is also obtained from patient medical records, specifically radiology reports and Dutch municipal personal records database (GBA).

Date of aneurysm rupture is obtained from patient medical records, specifically operative reports, radiology reports and progress notes.

Costs of all EVAR-related imaging and outpatient clinic visits will be calculated per patient. Cost is defined as volume times price. Prices from the ‘Cost manual of the Dutch Health Care Institute’’ will be used. Costs for the patients will also be included. The quality-adjusted life years, a generic measure of disease burden including both the quality and quantity of life, cannot be calculated with this retrospective design.

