### Sample size and power

Sample size calculation for this study is based on an expected difference of 7% in the proportions of patients not requiring interventions after 7 years between patients undergoing yearly standardised imaging surveillance (75% intervention-free rate^18^) versus those s not undergoing standardised imaging surveillance(82% intervention-free rate^19^). To detect this difference with 90% power and a 0.05 significance level, 719 patients per group are required and 1438 in total. To correct for the fact that the first CTA of approximately 20% of patients is abnormal, 1798 patients (1438/0.8) are needed.^20 21^ In addition, we expect incomplete data in 10% of the patients which results in a total number of 1997 patients (1798/0.9). With this sample size, we can also detect a 3% difference in aneurysm-related mortality with statistical significance. We chose a one-sided significance level (non-inferiority) of 0.05 and for standard proportion a 95% non-aneurysm-related mortality and thus 5% freedom from aneurysm-related mortality after 7 years: 0.95. For equivalence limit difference, we chose an acceptable difference between groups of 3%, in which if differences in aneurysm-related mortality equals 3%, they are considered non-inferior. Test-expected proportion is then equal to the standard proportion 0.97. Thus, the expected difference is 0, calculated with a power of 80%. This results in 653 patients per group and 1306 patients in total. Since the first CTA of approximately 20% of patients is abnormal, 1632 patients (1306/0.8) are needed. In addition, we expect incomplete data in 10% of the patients which results in a minimum of, 1813 patients (1632/0.9) are needed in total.

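### Groups A and B are formed from imaging gaps seen during follow-up but compared by Kaplan-Meier and log-rank as if known at baseline, so the mortality comparison carries immortal-time bias

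*Protocol article*

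**What the plan says.** General study design splits patients with a normal first postoperative CTA into group A (yearly imaging) and group B (no yearly imaging). The text below Figure 1 gives the criterion: "the definition of compliance is undergoing imaging surveillance every 16 months". Study procedures says how it is applied: "The time between imaging appointments is calculated to determine whether patients adhere to this studies definition". The same section defines the primary comparison as patients "who do adhere to our definition of yearly imaging surveillance over a 6-year to 11-year follow-up period" against those who do not.

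Statistical methods then treats the group as fixed from the start: "The primary endpoints, that is, survival and freedom from intervention will be estimated by Kaplan-Meier survival analysis". The two groups are tested against each other by log-rank. Freedom from rupture is handled in the same way. The Cox model is "corrected for age, gender, AAA diameter, ASA classification, neck length, neck angulation and type of endograft", all of which are known at or near the operation. The article states no landmark, no time-dependent exposure and no starting point for the clock. It does not say how to class a patient who dies or has an intervention before a 16-month gap could occur. The limitations in the Discussion cover retrospective records, transfers between centres and attrition, but not this problem.

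**The concern.** Under the gap rule a patient joins group B only by living through more than 16 months without imaging. Someone who dies before any such gap cannot be in B. Group B therefore carries a stretch of guaranteed survival, and the deaths that would have fallen in that stretch are counted elsewhere. A curve drawn from the operation treats the guaranteed stretch as time at risk. The distortion comes from how the groups are formed, so age, ASA class, neck anatomy or endograft type cannot correct it.

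Study objectives hypothesises that patients with less follow-up do better, and the Discussion intends the results to help surgeons decide on less follow-up. Sample size and power sets a 3-point non-inferiority margin for aneurysm-related mortality. A bias of similar size to that margin could produce non-inferiority, or refute it, without any effect of imaging.

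**Working it through.** **The plan's own figures.** Both sample sizes reproduce, so the stated rates are a sound basis.
- Superiority, 75% vs 82%, two-sided 0.05, 90% power: (1.960 + 1.282)² × (0.75×0.25 + 0.82×0.18) / 0.07² = 10.507 × 0.3351 / 0.0049 = 718.6, i.e. 719 per group.
- Non-inferiority, 95% in both groups, margin 3 points, one-sided 0.05, 80% power: (1.645 + 0.842)² × 2 × 0.95 × 0.05 / 0.03² = 6.183 × 0.095 / 0.0009 = 652.6, i.e. 653 per group.

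**Bias by hand.** Take 5% aneurysm-related mortality at 7 years (Sample size and power) and assume a constant hazard: h = −ln(0.95)/7 = 0.00733 per year. Suppose every group B patient stops imaging straight after the first CTA, which gives the shortest guaranteed stretch. B can have no deaths in the first 16 months (1.333 years), so its 7-year risk is 1 − exp(−0.00733 × 5.667) = 4.1% instead of 5.0%. The missing early deaths go to A if death before a gap counts as adherent, which pushes A above 5%. Later first gaps lengthen the guaranteed stretch and widen the difference.

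**Simulation with no effect of imaging.** From the documents: 5% aneurysm-related mortality at 7 years, the 16-month rule and long follow-up (simulated as about 7 to 12 years). Assumed, because the documents do not give them: all-cause mortality, and how scans are missed. Deaths before any gap are classed as adherent. The table shows 7-year aneurysm-related mortality.

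| Assumed imaging pattern | A | B | Spurious gap |
|---|---|---|---|
| Each yearly scan missed independently, 10%; all-cause mortality 40% at 7 years | 7.8% | 2.2% | 5.6 points |
| As above, 5–15% missed, all-cause mortality 30–50% | 6.2–10.5% | 2.0–2.4% | about 4 to 8 points |
| 50% stop early, the rest miss 2% per year | 6.3% | 3.8% | 2.5 points |
| 40% stop early, the rest miss 1% per year | 5.8% | 3.8% | 2.0 points |
| 40% stop early, the rest miss 5% per year | – | – | 3.4 points |

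Repeat runs of the early-stopping patterns with little later missing gave 1.9 to 2.7 points. A wider grid of independent missing, up to 20% of scans, took the gap to about 11 points. In that grid (8–20% missed, other-cause mortality 4–9% per year, 1438 patients) the log-rank test favoured B significantly in 92–100% of null replicates.

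**The other reading of adherence.** If adherent means scans completed through at least 6 years, early deaths fall into B. With 6% per year other-cause mortality and 12% missed scans, freedom from aneurysm-related death at 7 years is A 98.9% vs B 93.3%. The bias has reversed.

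**Intervention endpoint, no true effect.**
- Adherence judged to death or end of follow-up, imaging unchanged by intervention: 78.3% vs 78.6% intervention-free at 7 years (true rate 78.5%, the midpoint of 75% and 82%). With a true rate of 75%, it is 75.1% vs 75.1%. There is no bias.
- Adherence judged only up to the intervention: A 56–72% vs B 89–91%.
- Adherence judged past the intervention, with treated patients then missing half as many scans: 70.5% vs 79.7%.

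**After correction.** With follow-up split at the first gap, the null rates per year agree between A and B: aneurysm-related death 0.0074 vs 0.0073, all-cause death 0.0673 vs 0.0675, intervention 0.0346 vs 0.0346. A 2-year landmark gives 96.4% in both groups for freedom from aneurysm-related death. A 28-month landmark gives hazard ratios of 0.96–1.04.

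**The case against.** The strongest reply is that direction and size are not fixed by the text, and much of this stands.

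- **Direction.** The article never says that a patient who dies before a gap is adherent. A reader might infer that the bias always makes less imaging look safer. That follows from the literal gap rule, but the wording about a 6-to-11-year period also allows the reading under which it reverses.
- **Size.** A reader might infer a spurious gain that always exceeds the margin, or that a truly tripled hazard after a gap would be hidden. Both depend on scans being missed independently year by year. In that model a tripled hazard is masked (A 7.7% vs B 6.3%). If half the patients stop early it is visible (A 6.3% vs B 10.9%). Background and relevant literature and data makes persistent patterns plausible: protocols are hospital-specific, and one centre had already moved to imaging every 5 years.
- **Intervention.** The large differences need a rule that stops classification at the event, or more imaging after an intervention. The article states neither.
- **Cox model.** The form of the surveillance term is not given, so the article does not commit to a fixed one. The stated defect lies in the Kaplan-Meier and log-rank comparison.

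The core is untouched. The article itself names the exposure definition, the period over which it is judged, the estimator and the test. Together they produce the bias for mortality under either reading, so this is not a detail left to an analysis plan.

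**Conclusion.** The point holds for mortality-type endpoints: survival, aneurysm-related mortality and others of that kind are compared between groups that depend on later survival. Under the literal gap rule, with no true effect, the spurious difference in 7-year aneurysm-related mortality is about 2 to 8 points in favour of less imaging, against a 3-point margin. This rests on a constant hazard, assumed all-cause mortality of 30–50% at 7 years, and assumed patterns ranging from early stopping to 5–15% of scans missed independently. Heavier independent missing would enlarge it. If adherence requires at least 6 years of scans, the sign changes. For intervention, bias from this source is conditional, and it is absent if adherence is judged to death or end of follow-up and imaging does not change after an intervention. That bias exists for mortality is certain. Its sign and size depend on a classification rule and attendance data that the article does not give. It should be corrected before analysis.

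**What to change.** 1. Start the clock at the normal first CTA.
2. Make surveillance status a time-updated covariate in the primary Cox models. Every patient is adherent until the day 16 months have passed without surveillance imaging, and events before that day count as adherent. Count only imaging with a surveillance indication, done before the event. State whether a patient who resumes imaging becomes adherent again.
3. Replace the fixed-group Kaplan-Meier and log-rank comparison with a prespecified landmark analysis. For example, classify on the first 28 months (12 + 16) and include only patients alive and event-free at that point.

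The cost is revised wording in Statistical methods and modest programming. The secondary endpoints already list date and indication of all imaging, and dates of intervention, rupture and death. The downside is small: the landmark curves lose early events and address early adherence only, so the time-updated model has to carry the question about adherence over the whole follow-up.
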